#### Secondary outcome measures

##### Improvement of knee pain at 3, 6, 12, 18, and 24 months

Knee pain will be assessed using a 100 mm VAS by asking “on this line, thinking about your *right/left* knee, where would you rate your pain, using the last 7 days as a time frame”. We will also assess pain using WOMAC [49], as we used this instrument to demonstrate a clinically significant change in BML size (140 mm^2^) [11]. Five items of WOMAC pain scale in 100-mm visual analog format [50] will be used to assess pain during walking, using stairs, in bed, sitting or lying, and standing during the last 7 days. Items will be summed to create a total WOMAC pain score (range, 0–500). Incomplete items will be addressed according to the WOMAC user guide [51]. The WOMAC pain score will be considered invalid if there is more than one missing item. In the case there is only one missing item, the remaining four items will be averaged and then multiplied by five.

##### Reduction in BML size over 6 and 24 months (mm^2^)

BMLs will be defined as an ill-defined hyperintensity in the subchondral bone, on MRI. BMLs will be assessed on the sagittal proton density weighted sequences at the medial tibial, medial femoral, lateral tibial, lateral femoral and patella sites by means of image processing on an independent workstation using OsiriX software (University of Geneva, Geneva, Switzerland). The maximum size of each lesion will be measured in mm^2^ using software cursors applied to the greatest area of the lesion, as previously described in our pilot study [40]. Previously we have demonstrated an intraclass correlation coefficient (ICC) of 0.97 [11], using this method. Total BML size (mm^2^) will be calculated as the sum of every lesion within the medial tibial, medial femoral, lateral tibial, lateral femoral and patella sites at screening, 6 and 24 months.

#### Other measurements

##### Knee function

Knee function will be assessed using WOMAC [49] at months 0, 3, 6, 12, 18 and 24. Seventeen items of the WOMAC function scale in 100-mm visual analog format [50] will be used to assess function during descending stairs, ascending stairs, rising from sitting, standing, bending to floor/picking up an object, walking on flat surface, getting in/out of the car, going shopping, putting on socks/stockings, rising from bed, taking off socks/stockings, lying in bed, getting in/out of the bath, sitting, getting on/off the toilet, heavy domestic duties, and light domestic duties during the last 7 days. Items will be summed to create a total WOMAC function score (range, 0–1700). The WOMAC function score will be considered invalid if there are more than 2 missing items. In the case there are two or less missing items, the remaining items will be averaged and then multiplied by 17 [51].

##### The assessment of quality of life (AQoL)

Health related quality of life and utility will be assessed using The Assessment of Quality of Life (AQoL-4D) questionnaire [52] at 0, 6 and 24 months.

##### Co-pathology present on MRI

Cartilage defects will be assessed at the medial tibial, medial femoral, lateral tibial, lateral femoral and patella sites as we have previously described [53]: grade 0 = normal cartilage; grade 1 = focal blistering and intracartilaginous low-signal intensity area with an intact surface and base; grade 2 = irregularities on the surface or base and loss of thickness < 50%; grade 3 = deep ulceration with loss of thickness > 50%; and grade 4 = full-thickness chondral wear with exposure of subchondral bone. In our previous study we demonstrated the ICCs ranged from 0.80–0.95 [53] for the different knee sites, using this method.

Meniscal extrusion will be assessed as we have previously described [14] as the proportion of the menisci affected by a partial or full extrusion (yes/no) at the anterior, middle, and posterior horns (medially/laterally). In our previous study we demonstrated the intra and inter-reader ICC’s ranged from 0.85–0.92 for meniscal extrusion [54].

##### Knee surgery and joint injections

Whether the patient underwent any knee surgery (including arthroscopies or joint replacement surgery) during the trial, will be assessed by questionnaire at screening, month 3, 6, 12, 18 and 24 months. Study patients will also give their consent to have their data linked to the Australian Orthopaedic Association National Joint Replacement Registry (AOANJRR). Whether the patient had a joint injection during the trial will be assessed at month 6, 12, 18 and 24 months.

##### Lower limb muscle strength

Lower limb muscle strength is a key correlate of pain and tends to increase when pain is reduced [55]. We will assess leg strength by dynamometry at the lower limb (involving both legs simultaneously) at months 0, 6, 12 and 24. The muscles measured in this technique are mainly the quadriceps and hip flexors. The previously published repeatability estimate (Cronbach’s α) for this method is 0.91 [45].

##### Overall change in pain and function

At 24 months patients will be asked to rate their overall change in pain and function (compared to baseline) on this scale: Much Worse, Moderately Worse, Slightly Worse, No Change, Slightly Better, Moderately Better, and Much Better.

##### Anthropometry

We will measure height (stadiometer), weight (electric scales) and body mass index (BMI) (weight/height^2^) at month 0, 6, and 24 months.

##### Radiographic knee OA

A standing anteroposterior semiflexed radiograph of the study knee will be performed at screening. X-rays will be scored for joint space narrowing on a four point scale (0–3) using the OARSI atlas [43]. In our hands this method has very high reproducibility with an ICC of 0.98 for joint space narrowing and 0.99 for osteophytes [56].

##### Concomitant medication

There are no restrictions with regard to concomitant analgesic medications. Medication usage (including prescription, over-the-counter, and natural/herbal remedies) will be documented at screening, month 3, 6, 12, 18 and 24 months. Patients will be asked to keep medications as stable as possible but if there are changes to the medications used or dose changes during the trial the reason will be documented.

##### Blood samples

Blood tests (Urea Electrolytes and Creatinine (UEC), calcium and vitamin D assays) will occur for safety at screening to assess inclusion criteria. Storage of blood samples will occur at screening and 6 months for future testing at the following study sites: Hobart, Melbourne, and Sydney. The blood will be stored at − 80 °C.

##### Urine samples

Storage of first void fasting urine samples will occur at month 0 and 6 for future testing at the following study sites: Hobart, Melbourne, and Sydney. The urine will be stored at − 80 °C.

##### Treatment guessing

At 24 months patients will be asked what treatment they think they received with the following options: zoledronic acid (active treatment), placebo, or not sure.

##### Other site pain

Hand pain and low back pain will be assessed at months 0, 3, 6, 12, 18 and 24 using a 100 mm VAS by asking “on this line, thinking about your *most painful hand/low back*, where would you rate your pain, using the last 30 days as a time frame”.

### Safety assessment

Adverse events will be monitored throughout the study. Standard safety and efficacy monitoring will be performed through regular face-to-face visits and phone calls between visits. The patients are requested to report any adverse events to the research staff spontaneously. Details of the adverse event and its relationship with study intervention will be recorded and reported to the Ethics Committees.

Patients will be phoned 3 days following their infusion in order to determine if they have experienced any symptoms of acute phase reactions, including flushing, fever, joint pains, and muscle aches.

### Sample size calculations

#### Primary outcome

In our pilot study [40] we found that zoledronic acid significantly reduced the size of BMLs over 6 months compared to placebo. Therefore our sample size calculations for this trial were modelled based on the assumption that a decrease in BML size will translate to a reduction in cartilage volume loss over time. This assumption is valid based on the unequivocal evidence from observation data demonstrating that BMLs predict cartilage volume loss over time [14–17, 38, 54, 57–59].

The changes in BML area seen in our pilot study were − 198.6 mm^2^ (zoledronic acid treatment) and − 22.8 mm^2^ (placebo) with regression root mean square error of 261.5 mm^2^ (i.e. standard deviation (SD)) [40], at 6 months. Unpublished observational data from our Tasmanian Older Adult Cohort (TASOAC) study allowed us to model the effect a decrease in BML size would have on tibiofemoral cartilage volume loss over 24 months. Using follow-up data for 120 TASOAC participants with BMLs, we used linear regression to estimate the relationship between absolute change in tibiofemoral cartilage volume and final BML area with adjustment for age, sex, BMI and length of follow-up. The results can be used to predict each subject’s two-year change in tibiofemoral cartilage volume from their final BML area, and the change when final BML area is reduced by 198.6 mm^2^ (expected under treatment) or 22.8 mm^2^ (expected under placebo). To take account of individual variation, the calculations were repeated in 1000 replications with the exact changes in final BML area replaced by random values of 198.6 mm^2^ (treatment) firstly and 22.8 mm^2^ (placebo) secondly, and with SD 261.5 mm^2^ in each case. The resulting estimates of tibiofemoral cartilage loss, which are expected from the 6 month changes in BML area, were − 824.0 mm^3^ (SD 273.0) in the treatment group and − 928.3 mm^3^ (SD 272.3) in the placebo group. With this difference, 132 patients (allowing for 20% drop out over 24 months) recruited to each arm of the trial will provide 80% power with 5% probability of type I error (alpha = 0.05). This estimate is conservatively based on 6-month change in BML area for *n* = 59 patients in our pilot study [40] and assumes no further improvement in BMLs after this time (although they may continue to reduce with zoledronic acid over 24 months).

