**Methods:**

Two hundred sixty-four patients with clinical knee OA, significant knee pain and subchondral BMLs present on MRI will be recruited in Hobart, Melbourne, Sydney and Adelaide. They will be randomly allocated to the two arms of the study, receiving an annual identical intravenous infusion of either 100 mL of fluid containing zoledronic acid (5 mg/100 mL) or placebo (0.9% NaCl 100 mL), at baseline and 1 year later. MRI of the study knee will be performed at screening, month 6 and 24. Knee structure, symptoms and function will be assessed using validated methods. The primary outcome is absolute change in tibiofemoral cartilage volume (mm^3^) over 24 months. Secondary outcomes include improvement in knee pain over 3, 6, 12, 18, and 24 months and reductions in BML size over 6 and 24 months. The primary analyses will be intention-to-treat analyses of primary and secondary outcomes. Per protocol analyses will be performed as the secondary analyses.

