### Statistical analysis

The primary analyses will be intention-to-treat analyses of primary and secondary outcomes. Per protocol analyses will be performed as the secondary analyses.

Changes in absolute tibiofemoral cartilage volume, knee pain and BML size will be analysed using a linear mixed model with treatment, month and their interaction (treatment × month) as covariates. The correlation within trial centres and the repeated measures will be addressed using trial centre and patient identification as random intercepts. Month will be treated as random effect to allow different treatment effects among patients over time. Change in outcome measures within each group and difference of the changes between groups from baseline to follow-up will be calculated using linear combinations of the estimated coefficients. If there are baseline imbalances between treatment groups, we will consider adjusting for them based on whether we regard the imbalance as clinically significant. Missing data caused by loss to follow-up and nonresponses will be addressed by adding baseline complete variables that can explain the missingness to the regression models.

Secondary analysis for missing data will be performed using multiple imputation by chained equations. Baseline variables with complete data will be used for data imputation assuming missing at random.

Pre-specified stratified analyses will be performed to examine which subgroups may respond better to treatment. Potential stratification variables include radiographic knee OA and co-pathology present on MRI. Statistical significance will be set as a two-sided *P* value < 0.05.

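### The 80% power rests on SDs of regression-predicted cartilage loss; no step adding the residual variation of observed loss is described, so the stated power is unsupported and probably too high.

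*Protocol article*

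**What the plan says.** The abstract defines the endpoint as a measured quantity: "The primary outcome is absolute change in tibiofemoral cartilage volume (mm^3^) over 24 months".

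The article's sample size section (Primary outcome) reaches its inputs in three steps.

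- A linear regression in 120 cohort members with BMLs relates change in tibiofemoral cartilage volume to final BML area, with follow-up time, BMI, sex and age as adjustment variables. The article then says what this regression is for: "The results can be used to predict each subject’s two-year change in tibiofemoral cartilage volume from their final BML area".
- Final BML area is lowered by the pilot trial's mean change, 198.6 mm² for treatment or 22.8 mm² for placebo. To reflect individual variation, this is repeated 1000 times with the BML change drawn at random with SD 261.5 mm².
- The output of these replications is labelled "The resulting estimates of tibiofemoral cartilage loss, which are expected from the 6 month changes in BML area". For the two arms, the means and SDs reported under that label "were − 824.0 mm^3^ (SD 273.0) in the treatment group and − 928.3 mm^3^ (SD 272.3) in the placebo group".

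From that difference the section concludes that "132 patients (allowing for 20% drop out over 24 months) recruited to each arm of the trial will provide 80% power". It adds: "This estimate is conservatively based on 6-month change in BML area". The Statistical analysis section makes the test two-sided: "Statistical significance will be set as a two-sided *P* value < 0.05".

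Neither the residual SD nor R² of the cohort regression is given, nor the observed SD of cartilage change.

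**The concern.** A regression prediction varies less between patients than the outcome it predicts. The variance of observed change is the variance of the predictions plus the residual variance. The only random draw the article describes is on the predictor side (BML change). It describes no draw from the residual of the cartilage regression, and gives no other SD for the power statement.

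That residual cannot be zero. The Primary outcome measure section reports reading CVs of 2.1% and 2.2% for the tibial plates and about 2% for the femur, before any unexplained difference between patients.

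The planned analysis does not clearly remove the variance either. The mixed model has treatment, month and their interaction as covariates. Other baseline variables enter only if an imbalance is judged clinically significant or if they explain missingness, so adjustment for age, sex or BMI is not assured.

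At stake is the meaning of the trial's headline design claim. If the true SD is larger, 264 patients have less than 80% power for 104.3 mm³, and a non-significant primary result would be weaker evidence against a structural effect than the article suggests.

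**Working it through.** **Inputs from the article.** Difference Δ = 928.3 − 824.0 = 104.3 mm³. Pooled SD = √((273.0² + 272.3²)/2) = 272.65 mm³. Completers per arm n = 132 × 0.8 = 105.6. Two-sided α = 0.05. Power is for a two-sample t-test with noncentrality Δ/(S√(2/n)); a normal approximation differs by less than half a percentage point.

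**Reproducing the stated figure.** Noncentrality = 104.3/(272.65 × 0.1376) = 2.78, so power is 79%. In the other direction, 80% power needs 108 evaluable per arm, or 108/0.8 = 135 recruited, against 132 stated. The arithmetic agrees with the article to within rounding, and the 80% rests wholly on the SD of about 273.

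**What that SD contains.**

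- Implied slope: 104.3/(198.6 − 22.8) = 0.593 mm³ per mm².
- Simulated BML change: 0.593 × 261.5 = 155 mm³.
- Remainder: √(272.65² − 155²) = 224 mm³, which the members' spread in covariates and BML area could supply.
- If 273 were instead the spread of replicate means over 120 members, the BML draws would give only 155/√120 = 14 mm³. So 273 is a between-subject SD.

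**Adding a residual.** S = √(272.65² + r²), where r is the residual SD. The article does not give r, so these values are assumptions. The last column is (1.96 + 0.842) × S × √(2/105.6).

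| Assumed r (mm³) | S (mm³) | Power for 104.3 mm³ | Difference detectable with 80% power (mm³) |
|---|---|---|---|
| 0 (as described) | 273 | 79% | 105 |
| 100 | 290 | 74% | 112 |
| 150 | 311 | 68% | 120 |
| 200 | 338 | 61% | 130 |
| 300 | 405 | 46% | 156 |

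**The same by assumed R² of the cohort regression.** This takes the 224 mm³ as the SD of the cohort's fitted values, so r = 224√((1 − R²)/R²). The lenient column treats the simulated BML variation as already part of the cohort's own variance, so S = 224/√R².

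| Assumed R² | r (mm³) | S (mm³) | Power | Lenient S (mm³) | Lenient power |
|---|---|---|---|---|---|
| 0.5 | 224 | 353 | 57% | 317 | 66% |
| 0.3 | 342 | 438 | 41% | 409 | 45% |
| 0.2 | 448 | 525 | 30% | 501 | 32% |

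On the lenient reading, 80% is reached at R² of about 0.7 (S = 268).

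**Reading error alone, as an order of magnitude.** Assume a CV of 2%, four equal plates with independent errors, and total volume V (not in the article). The SD of a change score is √2 × 0.02 × V/√4. V = 6,000, 10,000 or 15,000 mm³ gives 85, 141 or 212 mm³, and power 75%, 69% or 59%. Reading error is part of the residual, so it must not be added to the tables above.

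**The case against.** The strongest reply is that the size of the shortfall cannot be derived. RMSE and R² are not reported, the cohort analysis is unpublished, and the article condenses it. A residual may have been drawn without being mentioned. This stands as a limit on the size. It does not supply the missing step: the simulation is described in some detail, and the one source of individual variation named is the BML change.

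Four stronger readings are tempting, and the article does not support them.

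- *The 80% holds only if the regression explains all the variation.* This is too absolute. The simulated BML variation is added to members whose final BML areas already differ. If it is counted as part of the cohort's variance, R² of about 0.7 is enough.
- *The 273 splits into BML noise and covariates, with nothing left for residual error.* The 224 mm³ is a remainder obtained by subtraction. The article gives no covariate SD, so the split cannot show that no residual is inside it. The evidence is the described procedure.
- *Observed SD is 272.65/√R².* This also inflates the simulated BML variation, which is not part of the cohort's fitted variance. It gives powers that are too low (50% at R² = 0.5, where √(272.65² + r²) gives 57%).
- *The article calls its variance conservative.* It does not. That word concerns the use of the 6-month BML effect with no later improvement, and in that sense it is coherent. A reader could still carry it over to the whole calculation.

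**Conclusion.** The point holds. By the procedure described, the SDs behind "80% power with 5% probability of type I error (alpha = 0.05" are SDs of predicted cartilage loss, while the endpoint is observed loss. The stated inputs give 79% with no margin, so if nothing else changes, any residual added to the stated SD takes power further below the target.

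How far below is conditional. For assumed residual SDs of 100 to 300 mm³ power is 74% to 46%. For an assumed R² of 0.5 or lower it is at most 57%, or at most 66% on the lenient reading. The stated power could be about right if residuals were drawn but not reported, or if, on the lenient reading, BML area and the four adjustment variables explain about 70% of the variance in cartilage change. The article claims neither.

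Confidence is high that the described method lacks a residual term and only moderate on the size of the loss. The design, endpoint and analysis model are not themselves at fault here.

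**What to change.** - Recompute with SD = √(273² + RMSE²), where RMSE is the residual SD of the same 120-member regression, or with the observed SD of 24-month change in tibiofemoral cartilage volume. A blinded pooled SD from the trial could serve as a check.
- Report that SD, and restate either the power of 264 patients for 104.3 mm³ or the difference detectable with 80% power.
- Make clear that *conservatively* refers only to carrying the 6-month BML effect forward and not to the variance.
- If residuals were in fact drawn in the 1000 replications, say so and give their SD. That would close the point.
- State that a non-significant primary result will be read through its confidence interval.

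The cost is one rerun of an existing regression and a few sentences. No extra patients or data are needed. The downside is a less favourable stated power.

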#### Secondary outcome

For our secondary outcomes (improvement in pain and reduction in BML size) a sample size of 132 patients in each arm will provide 98.9 and 99.6% power to detect the adjusted treatment differences in knee pain scores and BML area respectively that were observed in our pilot study [40].

### Statistical analysis

The primary analyses will be intention-to-treat analyses of primary and secondary outcomes. Per protocol analyses will be performed as the secondary analyses.

Changes in absolute tibiofemoral cartilage volume, knee pain and BML size will be analysed using a linear mixed model with treatment, month and their interaction (treatment × month) as covariates. The correlation within trial centres and the repeated measures will be addressed using trial centre and patient identification as random intercepts. Month will be treated as random effect to allow different treatment effects among patients over time. Change in outcome measures within each group and difference of the changes between groups from baseline to follow-up will be calculated using linear combinations of the estimated coefficients. If there are baseline imbalances between treatment groups, we will consider adjusting for them based on whether we regard the imbalance as clinically significant. Missing data caused by loss to follow-up and nonresponses will be addressed by adding baseline complete variables that can explain the missingness to the regression models.

Secondary analysis for missing data will be performed using multiple imputation by chained equations. Baseline variables with complete data will be used for data imputation assuming missing at random.

Pre-specified stratified analyses will be performed to examine which subgroups may respond better to treatment. Potential stratification variables include radiographic knee OA and co-pathology present on MRI. Statistical significance will be set as a two-sided *P* value < 0.05.

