### Randomisation and blinding

Allocation of patients in a 1:1 ratio to either the active or placebo group will be based on computer generated random numbers using a central randomisation website hosted by the University of Tasmania. Block randomisation, using a block size of 10 (5 in each arm) will be used. This means that of every 10 patients randomised, 5 will receive active and 5 placebo. The randomisation will be stratified by study site. This will be conducted by a staff member at each study site with no direct involvement in the study.

The randomised controlled trial will be a double-blind one, with both patients and investigators assessing outcomes blinded to treatment allocation. Allocation concealment and double blinding will be ensured by 1) the use of identical IV infusions for each group; 2) objective measures of knee structural changes being made by trained observers blinded to group allocation; and 3) subjective measures being taken by research nurses blinded to group allocation.

Emergency unblinding will be allowed in limited situations that impact on the safety of study patients. Code-break for the full randomisation schedule will be maintained by the University of Tasmania. Patients who are unblinded will be withdrawn from treatment but will continue to be followed as per the planned follow-up schedule.

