### Outcome measures

#### Primary outcome measure: Absolute change in tibiofemoral cartilage volume (mm^3^)

Knee MRI acquisition at the four study sites is presented in Table 2, including details of sequences and parameters being used. Tibial cartilage volume will be assessed on the sagittal T1-weighted sequences by means of image processing on an independent workstation using OsiriX software (University of Geneva, Geneva, Switzerland). The volumes of tibial cartilage plates (medial tibia and lateral tibia) will be isolated from the total volume by manually drawing disarticulation contours around the cartilage boundaries on a section by section basis. These data will then be re-sampled by means of bilinear and cubic interpolation for final 3-D rendering. In our previous study, we demonstrated a coefficient of variation (CV) of 2.1% for the medial tibia and 2.2% for the lateral tibia [45], using this method.

**Table 2 Tab2:** Magnetic resonance imaging sequences and parameters at the four study sites

	Machine and coil	T1-weighted sagittal	Proton density-weighted sagittal
Hobart (Note: used two different MRI scanners. Patients had their follow-up scans on the same scanner in which they had their screening scan).	1.5 T whole-body MR unit (GE Optima 450 W, Milwaukee, USA), using a dedicated 8-channel knee coil 1.5 T whole-body MR unit (Siemens, Espree), using a dedicated 15-channel knee coil	T1-weighted fat-saturated 3D gradient-recalled acquisition; flip angle 30 degrees; repetition time 38 msec; echo time 3 msec; field of view 16 cm; 512 × 512 matrix; 1 excitation; slice thickness 1.5 mm T1-weighted fat-saturated 3D gradient-recalled acquisition; flip angle 30 degrees; repetition time 31 msec; echo time 6.8 msec; field of view 16 cm; 512 × 512 matrix; 1 excitation; slice thickness 1.5 mm	Proton density fat-saturated 2D fast spin echo sequence; flip angle 150 degrees; repetition time 3800 msec; echo time 35 msec; field of view 16 cm; 512 × 512 matrix; 3 excitations; slice thickness 3 mm Proton density fat-saturated 2D fast spin echo sequence; flip angle 150 degrees; repetition time 3830 msec; echo time 39 msec; field of view 16 cm; 512 × 512 matrix; 3 excitations; slice thickness 3 mm

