Melbourne	3.0 T whole-body MR unit (Philips, Achieva, Medical Systems), using a commercial 16-channel transmit receive knee coil	T1-weighted fat-saturated 3D gradient-recalled acquisition; flip angle 15 degrees; repetition time 25.9 msec; echo time 9.2 msec; field of view 16 cm; 320 × 320 matrix; slice thickness 0.5 mm	Proton density fat-saturated 2D fast spin echo sequence; flip angle 90 degrees; repetition time 3814 msec; echo time 25 msec; field of view 16 cm; 720 × 720 matrix; slice thickness 2.5 mm
Sydney	1.5 T whole-body MR unit (Siemens, Aera) using a dedicated 15-channel transmit-receive knee coil	T1-weighted fat-saturated 3D gradient-recalled acquisition; flip angle 30 degrees, repetition time 31 msec; echo time 6.8 msec; field of view 16 cm; 512 × 512 matrix; slice thickness 1.5 mm	Proton density fat-saturated 2D fast spin echo sequence; flip angle 150 degrees; repetition time 3830 msec; echo time 39 msec; field of view 16 cm; 512 × 512 matrix; slice thickness 3 mm
Adelaide	1.5 T whole-body MR unit (Siemens, Aera) using a dedicated 15-channel transmit-receive knee coil	T1-weighted fat-saturated 3D gradient-recalled acquisition; flip angle 30 degrees, repetition time 14.7 msec; echo time 6.74 msec; field of view 16 cm; 448 × 448 matrix; 1 excitation; slice thickness 1.5 mm	Proton density fat-saturated 2D fast spin echo sequence; flip angle 180 degrees; repetition time 3200 msec; echo time 39 msec; field of view 16 cm; 320 × 320 matrix; 1 excitation; slice thickness 3 mm

Knee femoral cartilage volume will be determined on the sagittal T1-weighted sequences by means of image processing on an independent workstation using Cartiscope™ (ArthroLab Inc., Montreal, Quebec, Canada), as previously described [46–48]. The segmentation of the cartilage-synovial interfaces will be carried out with the semi-automatic method under reader supervision and with corrections when needed. Cartilage volume will be evaluated directly from a standardised view of 3D cartilage geometry as the sum of elementary volumes. In our previous study, we demonstrated a CV of approximately 2% [46]. The cartilage volume assessment will be done for the medial and lateral condyles delineated by the Blumensaat’s line [48].

Tibiofemoral cartilage volume will be calculated as the sum of both the tibial and femoral compartments at screening and 24 months.

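### Site stratifies the randomisation but enters the model only as a random intercept, which cancels out of change, so the primary contrast is unadjusted for site; if sites differ in mean change, the analysis is conservative and loses a little power.

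*Protocol article*

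**What the plan says.** Under Randomisation and blinding, allocation is 1:1 in blocks of 10, and "The randomisation will be stratified by study site". There are four sites, each aiming for 66 patients (Study design).

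Under Statistical analysis, the linear mixed model has treatment, month and their interaction as covariates. Site appears in one place: "The correlation within trial centres and the repeated measures will be addressed using trial centre and patient identification as random intercepts". The next sentence makes month a random effect and describes it as varying among patients. The treatment effect is the between-group difference in change from baseline, built from linear combinations of the coefficients. Neither site-by-month nor scanner is listed. Baseline adjustment is considered only where an imbalance is judged clinically significant.

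The primary outcome section computes tibiofemoral volume at screening and 24 months only. Table 2 shows that acquisition differs by site. Melbourne has a "3.0 T whole-body MR unit (Philips, Achieva, Medical Systems" scanner with 0.5 mm slices on the T1-weighted sequence used for cartilage; the other sites have 1.5 T and 1.5 mm slices. Hobart "used two different MRI scanners", with each patient kept on the one used at screening.

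**The concern.** When randomisation is balanced within sites, differences between sites in the outcome no longer contribute to the chance error of the treatment comparison. The analysis has to remove them too; otherwise they stay in the residual and the reported standard error is larger than the true one.

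Here the outcome that matters is change. Volume of patient i at site s is modelled as a mean plus a centre intercept a_s, a patient intercept, and so on. Subtracting the screening value from the 24-month value removes a_s. The only term that represents the stratification factor therefore does nothing for the contrast on which the primary hypothesis rests. Any site difference in mean cartilage loss, from case mix or from how a scanner and sequence scale measured volume, stays in the error.

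At stake are efficiency and calibration: confidence intervals wider than necessary and some lost power, in a trial sized with no margin above 80%.

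**Working it through.** **Inputs from Sample size calculations.** Expected changes are −"824.0 mm^3^ (SD 273.0) in the treatment group" and −"928.3 mm^3^ (SD 272.3) in the placebo group". The plan states that 132 per arm with 20% dropout "will provide 80% power with 5% probability of type I error (alpha = 0.05"; Statistical analysis makes the test two-sided.

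- Difference: 928.3 − 824.0 = 104.3 mm³.
- Pooled SD: √[(273.0² + 272.3²)/2] = 272.65 mm³.
- Evaluable per arm: 132 × 0.8 = 105.6.

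**The plan's own figure.** n = 2(1.960 + 0.842)² × 272.65²/104.3² ≈ 107.3, so 108 per arm. Dividing by 0.8 gives 135; multiplying by 1.2 gives 130. The stated 132 is within 3% of both. At 105.6 per arm, SE = 272.65 × √(2/105.6) = 37.52 and power = Φ(104.3/37.52 − 1.960) = Φ(0.820) = 79.4%. The stated sample size is reproduced.

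**Does the centre intercept touch the contrast?** Three trials were simulated with 4 sites of 66, blocks of 10, 20% dropout and a between-site share of 10% of the variance of change. Standard errors of treatment × month without and with a random centre intercept were 36.128 and 36.128; 36.305 and 36.303; 35.915 and 35.914. The estimate moved by at most 0.2 mm³. The intercept does not adjust change for site.

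**Size.** Let f be the share of the variance of 24-month change that lies between sites. The documents do not give f, so it is an assumption. Hold the total SD at 272.65 and write z = 1.960.

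- Model SE without site adjustment of change: M = 37.52.
- True SE under site-stratified randomisation: T = M√(1 − f).
- Type I error: 2[1 − Φ(zM/T)].
- Power unadjusted: Φ((104.3 − zM)/T). Power adjusted: Φ(104.3/T − z).

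| f (assumed) | T | M/T | Type I error | Power unadjusted | Power adjusted | Gain (points) |
|---|---|---|---|---|---|---|
| 0 | 37.52 | 1.000 | 5.0% | 79.4% | 79.4% | 0 |
| 0.05 | 36.57 | 1.026 | 4.4% | 80.0% | 81.4% | 1.4 |
| 0.10 | 35.60 | 1.054 | 3.9% | 80.6% | 83.4% | 2.8 |
| 0.15 | 34.59 | 1.085 | 3.4% | 81.3% | 85.4% | 4.1 |

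Unadjusted power also rises with f, because stratified allocation already removes between-site variance from the true error. The gain must therefore be read across a row, not against 79.4%. A simulation of 6,000 trials per setting agrees: at f = 0.10, type I error is 4.1% unadjusted and 5.1% adjusted, and power 80.0% and 83.2%.

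**If 272.65 is instead the within-site SD.** This is conceivable, since the figure was modelled from one Tasmanian cohort. Unadjusted power is then 77.9% at f = 0.05 and 76.2% at f = 0.10, against 79.4% with adjustment.

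**How large a site difference does f imply?** If one of four equal sites differs from the other three by D, the between-site variance is (1/4)(3/4)D² = 3D²/16, so D = 272.65√(16f/3). For f = 0.05, 0.10 and 0.15, D is 141, 199 and 244 mm³. That is 16%, 23% and 28% of the mean expected loss, (824.0 + 928.3)/2 ≈ 876 mm³. A 5% scaling difference at one site (assumed) gives D ≈ 44 mm³ and f ≈ 0.5%.

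**The case against.** **The site differences may be small.** The documents give no between-site variance of change. Patients at Hobart stay on their screening scanner and the other sites list one scanner each, so a constant scanner offset cancels out of change. What can remain is proportional scaling, differing measurement error, or case mix. As shown above, shares of 5% to 15% need sizeable differences in mean loss. This stands: the loss is conditional and may be negligible.

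**Change may be the response.** The model paragraph opens by speaking of changes being analysed. If 24-month change is the response, a centre intercept does adjust it and most of the point disappears. That reading fits poorly with a patient intercept, a month term and only two MRI time points for the primary outcome, but the article does not rule it out. One might add that a variance from four centres would often be estimated as zero, so site would drop out anyway. With about 53 evaluable patients per site, the chance of a zero estimate is about 15%, 7% and 4% at f = 5%, 10% and 15%. It is common (about 61%) only at f = 0, where nothing is lost. Having few centres is not the cause of the problem.

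**Model detail belongs in the analysis plan.** Scanner terms and variance structures may well be there. But the article does fix how centre enters, and that stated choice is what is at issue.

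**Stronger readings.** A reader might infer that standard errors are wrong whatever the data, that the result would be biased, or that false positives would increase. None of these follows. The mismatch needs site differences in mean change, the treatment estimate is unbiased, and type I error falls below 5%. Nor does leaving out scanner within Hobart conflict with the design, because scanner is not a stratum.

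**Conclusion.** The point holds as a minor flaw of efficiency and calibration, not of validity. On the natural reading, the primary contrast is not adjusted for the stratification factor. The consequence is a standard error about 3% to 8% too large and a power loss of 1.4 to 4.1 points, at assumed between-site shares of 5% to 15%. The loss is zero if mean change does not differ by site.

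The conclusion rests on the mixed model being fitted to volumes rather than to change, on the plan's own difference and SD with 20% dropout, on equal dropout across arms and sites, and on a site share that the documents do not supply.

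**What to change.** In Statistical analysis, replace the random centre intercept with fixed effects for site and site-by-month in the repeated-measures model. If 24-month change is meant to be the response, say so and include site as a fixed effect. Either version also settles whether levels or change are modelled.

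For the primary outcome, with two time points, the cost is three degrees of freedom on the change contrast (four sites less one) out of about 211 evaluable patients (2 × 105.6). No extra data are needed. It should be settled before unblinding.

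Splitting Hobart by scanner, and letting the residual variance of MRI outcomes differ by scanner, are reasonable sensitivity analyses but optional.
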